## Abstract

**Introduction:**

Stroke is a major cause of death and disability worldwide, frequently resulting in persistent cognitive deficits among survivors. These deficits negatively impact recovery and therapy engagement, and their treatment is consistently rated as high priority by stakeholders and clinicians. Although clinical guidelines endorse cognitive screening for poststroke management, there is currently no gold-standard approach for identifying cognitive deficits after stroke, and clinical stroke services lack the capacity for long-term cognitive monitoring and care. Currently, available assessment tools are either not stroke-specific, not in-depth or lack scalability, leading to heterogeneity in patient assessments.

**Methods and analysis:**

To address these challenges, a cost-effective, scalable and comprehensive screening tool is needed to provide a stroke-specific assessment of cognition. The current study presents such a novel digital tool, the Imperial Comprehensive Cognitive Assessment in Cerebrovascular Disease (IC3), designed to detect both domain-general and domain-specific cognitive deficits in patients after stroke with minimal input from a health professional. To ensure its reliability, we will use multiple validation approaches, and aim to recruit a large normative sample of age-matched, gender-matched and education-matched UK-based controls. Moreover, the IC3 assessment will be integrated within a larger prospective observational longitudinal clinical trial, where poststroke cognition will be examined in tandem with brain imaging and blood biomarkers to identify novel multimodal biomarkers of recovery after stroke. This study will enable deeper cognitive phenotyping of patients at a large scale, while identifying those with highest risk of progressive cognitive decline, as well as those with greatest potential for recovery.

**Ethics and dissemination:**

This study has been approved by South West—Frenchay Research Ethics Committee (IRAS 299333) and authorised by the UK’s Health Research Authority. Results from the study will be disseminated at conferences and within peer-reviewed journals.

**Trial registration number:**

NCT05885295. Stage: Pre-results.

STRENGTHS AND LIMITATIONS OF THIS STUDYA major methodological strength of the study involves the development of the first digital screening technology that allows remote monitoring of stroke-specific cognitive deficits in a manner that is cost-effective and suitable for large-scale population-based investigations.Through its digital and conventional assessments, the current study provides a scalable yet deep cognitive phenotyping of both domain-specific and domain-general impairments, longitudinally mapping poststroke recovery trajectory.A particular strength of the study is the comprehensive collection of multimodal data (behaviour, brain imaging and blood) that allows the development of novel quantifiable biomarkers of poststroke recovery.A limitation of the digital assessment is that it is designed to target stroke survivors with mild to moderate cognitive impairment, thus likely will have limited applicability in patients with severe deficits.While the use of technology to administer unsupervised cognitive assessments at a large scale facilitates improved diagnostic and monitoring capabilities, it may also lead to systematic exclusion of those with limited access to technology.

## Introduction

Stroke is a leading cause of death and disability globally, with frequent cognitive sequalae affecting three-quarters of survivors.^1^ The spectrum of cognitive deficits includes background ‘vascular cognitive impairment’ and more domain-specific deficits, such as aphasia which affects one-third of patients.^2^ Collectively, these impairments negatively impact poststroke recovery and engagement with therapy.^3^ Furthermore, there is a high failure rate of poststroke cognitive rehabilitation trials, due to our poor understanding of individual patient-level mechanisms of poststroke cognitive recovery and the ensuing inadequate stratification of both treatment responders and non-responders in the same clinical trials. It is, therefore, important to understand the factors that affect cognitive recovery poststroke, a topic increasingly recognised by funders and stakeholders as a high priority research area.^4–6^

Although clinical guidelines have been recently updated to recommend cognitive screening for poststroke management, there is currently no gold-standard approach for identifying cognitive deficits after stroke.^7^ Clinicians and researchers often select cognitive tests depending on preference, familiarity and availability, leaving little prospect for generalisability of their findings. Moreover, clinical stroke services do not have the capacity to provide long-term cognitive monitoring and care for stroke survivors who have unpredictable recovery trajectories.^3 8^ This challenge is further compounded by the lack of cost-effective cognitive tools suitable for long-term monitoring, and the reliance of such monitoring on resource-stretched healthcare professionals.

Availability of a cost-effective, reliable and comprehensive screening tool that provides a stroke-specific deep phenotyping of cognition would be a game-changer. In the clinical setting, it would improve the detection rate and monitoring of cognitive deficits poststroke, and in the research setting, it would facilitate much needed large-scale population-based mechanistic studies aimed at understanding the mechanisms of cognitive recovery. Here, we present such a novel digital adaptive tool: The Imperial Comprehensive Cognitive Assessment in Cerebrovascular Disease (IC3). IC3 is a digital assessment designed to require minimal input from a clinician in detecting both domain-general and domain-specific cognitive deficits in patients after stroke. To ensure its reliability, several validation studies will be conducted against established clinical screening tools, and normative samples will be computed using representative age-matched, gender-matched and education-matched UK-based controls.

In line with recent efforts in identifying biomarkers of poststroke recovery,^9^ the IC3 tool will be integrated within a larger prospective longitudinal clinical study, where poststroke cognition will be examined in tandem with brain imaging and novel blood biomarkers. This study is entitled ‘understanding factors affecting cognitive function in cerebrovascular disease’ and will hereafter be referred to as the ‘main study’.

## Methods and analysis

### Aims

Develop an adaptive, scalable, self-administered, digital comprehensive cognitive screening tool to detect cognitive impairments in patients with cerebrovascular disease. The IC3 will:Detect both domain-general (eg, executive function) and domain-specific (eg aphasia, apraxia, neglect) deficits poststroke.^10^Allow monitoring to occur at scale, in a cost-efficient manner, as test administration can occur independent of trained professionals.Minimise the effects of neglect or aphasia on cognitive assessments.Have high test–retest reliability for repeated-testing longitudinally.Validate the IC3 against commonly used cognitive screening tools.Use IC3 in a cohort of stroke survivors to map the cognitive recovery trajectory over the course of the first year after stroke.Identify novel biomarkers of cognitive outcome (at 1 year) and recovery trajectory through the main study using:Demographics, and comorbid physical, neuropsychological and socioeconomic factors.Structural and functional MRI brain imaging, to assess metrics of cerebrovascular disease load, stroke lesion topology and brain network dynamics.Blood biomarkers of Alzheimer’s disease (phosphorylated tau forms and amyloid β42/40 ratio), neuroaxonal injury (neurofilament light, NFL and brain-derived tau) and astrocytic activation (glial fibrillary acidic protein, GFAP). The study will characterise the time course of these biomarkers over the first year after stroke and relate these to MRI measures of axonal injury and brain atrophy, as well as cognitive and functional outcomes.

### IC3 assessment design and development

#### Cognitive tests

The IC3 assessment covers 22 short tasks, spanning a wide range of cognitive domains (table 1), followed by several clinically validated questionnaires, designed to be completed in under 60–70 min. IC3 has in-built automated break reminders every 20 min with the additional option to take an unscheduled break at any time. IC3 is available via a web-browser on any modern device (smartphone, tablet, computer/laptop) by clicking on a link created by the study team. The IC3 test is implemented via Cognitron, a state-of-the art platform for remote neuropsychological testing rapidly being adopted by large scale population studies both in the UK and internationally.^11^

**Table 1 T1:** Tasks tested in the IC3 and their associated cognitive domain

Cognitive domain			Task name
Primary	Secondary	Tertiary	
Attention	Spatial ability	Space	Pear cancellation (visual-spatial ability)
		Object	
	Auditory sustained attention		Auditory attention task
	Visual sustained attention	Simple upper-limb movement	Simple reaction time
Executive	Task switching and attention		Non-verbal trail making (task switching)
	Reasoning	Mental shifting and flexibility	Rule finding
			Odd one out (pattern recognition)
		Spatial planning	Blocks
Language	Speech production	Phonology and semantics	Naming
		Phonology	Repetition
		Phonology, fluency and semantics	Spoken picture description
		Reading	Reading
	Semantics	Verbal semantics	Semantic judgement
	Comprehension (word-picture or word-sentence matching)	Auditory and orthographic processing	Language comprehension
Memory	Long term		Orientation
	Short term	Verbal working memory	Digit span
		Visuo-spatial working memory	Spatial span
		Visuospatial memory	Paired sssociates learning
	Episodic	Visuospatial	Task recall
		Verbal	Target word recall from auditory attention test
No skills			Graded calculation
Praxis	Ideomotor action semantics		Gesture recognition
Motor ability	Left-right upper-limb movement	Attention	Choice reaction time (click on left or right side of the screen)
	Multi-directional upper-limb movement		Motor control (click on moving target)

IC3, Imperial Comprehensive Cognitive Assessment in Cerebrovascular Disease.

The digital nature of the IC3 affords scalability in cognitive monitoring by being usable in both the clinical setting and home environment in the absence of a trained clinician. As well as reducing healthcare costs, this feature promotes accessibility of the assessment for physically disabled patients in whom attendance to healthcare or research setting is difficult. Compared with pen-and-paper tests, the IC3 test administration is standardised, more detailed response metrics per individual tests are provided (eg, accuracy, reaction time and trial-by-trial variability) and real-time patient scores are calculated automatically against a large age-matched, education-matched and sex-matched control sample. The IC3 specifications are summarised in figure 1.

**Figure 1 F1:**
[figure not shown]
Infographic outlining the main specifications of the IC3 digital cognitive testing. IC3, Imperial Comprehensive Cognitive Assessment in Cerebrovascular Disease.

#### Demographic and neuropsychiatric questionnaires

A number of health questionnaires and modified versions of relevant clinically validated questionnaires are completed by the patient or carers, including Apathy Evaluation Scale,^7^ Fatigue Severity Scale,^12^ Geriatric Depression Scale,^13^ Instrumental Activities of Daily Living (see table 2). On completion of the cognitive tests, the participants also fill in modified versions of relevant clinically validated questionnaires, including Modified short version of Apathy Evaluation Scale,^7^ Modified short version of Fatigue Severity Scale,^12^ Short form of the Geriatric Depression Scale,^13^ Instrumental Activities of Daily Living.^14^

**Table 2 T2:** Questionnaire items included in the IC3

	Range/categories
Age	0–100
Biological sex	Male/female
Years of education	Forced choice answers scaled to 0–21
Handedness	Likert scale ranging from 1 to 5, where 1 is right handed, 3 is ambidextrous and 5 is left handed
Hand used for making responses	Left/right
Hand impairments	Yes/no
English proficiency	Native, excellent but non-native, moderate level, low level
Ethnicity	White, Asian, black, Arab, mixed, other
Occupational status	Unemployed, long-term sick, retired, student, self-employed, employed
Annual income	£0–£100 000+
Existence of stroke risk factors	Diabetes, high-blood pressure, high cholesterol, heart disease, kidney disease, alcohol dependency, over-weight, smoker, ex-smoker
Existence of medical conditions (followed by more probing questions if an option is selected)	Stroke, other neurological problems, depression, anxiety
If participant indicates a history of stroke	
How long ago was the stroke?	Date/time
How many strokes	0–10
Type of stroke	Ischaemic, haemorrhagic, Transient Ischaemic Attack, subarachnoid haemorrhage, I don’t know
Problems caused by the stroke	Language, memory, concentration, movement of the right arm/leg, movement of the left arm/leg, vision, other
Movement	Difficulties in standing, sitting and in sit-to-stand

IC3, Imperial Comprehensive Cognitive Assessment in Cerebrovascular Disease.

At the end of the assessment, the participant will be given a graphical, easy-to-understand diagram that highlights their performance against normative data (figure 2). The normative data will be based on single time point data collected remotely from 5000 healthy controls. For tasks with normally distributed data, mild, moderate and severe impairment will be classed using suggested cut-offs of −1.5 to –2.0 and −2.5 SD below the mean, respectively. For tasks with ceiling effects, 90th, 95th and 99th percentiles are the suggested cut-offs.

**Figure 2 F2:**
[figure not shown]
Example of cognitive summary report. Patient’s performance (in purple) is outlined against a normative group (in grey), corrected for device, age, gender and education. Each interval spacing represents 0.5 SD units (SD) such that this participant’s language comprehension performance was 1.5 SD below the mean normative performance. On the periphery of the spider diagram, the percentile score is shown for each task in purple, alongside a graded level of impairment.

#### Main IC3 study design

This prospective observational longitudinal study aims to recruit 300 patients with acute stroke and obtain repeated measures of cognition and psychosocial status at baseline, 3 months, 6 months and 12 months postictus. IC3 is currently a single-site study at Imperial College Healthcare NHS Trust, England, and commenced recruitment in February 2022. In addition to the cognitive monitoring, all patients will be invited to take part in MRI brain imaging and blood biomarker substudies (figure 3; see substudies for more details).

**Figure 3 F3:**
[figure not shown]
(A) Overview of the main IC3 study and data collection. (B) Patient recruitment progress between February 2022 and March 2023. Cognitive assessments will be performed using the IC3 online assessment. Additional substudies will include blood biomarkers and MRI brain imaging. The 1-year follow-up is expected to take place between 12 months and 24 months poststroke.C3, Imperial Comprehensive Cognitive Assessment in Cerebrovascular Disease.

#### IC3 validation substudy

A minimum of 100 patients will undergo clinically validated pen-and-paper cognitive screens used routinely in clinical practice including the Montreal Cognitive Assessment (MOCA),^15^ star cancellation task^16^ and/or the Oxford Cognitive Screen (OCS). Sensitivity, specificity analyses, as well as convergence and divergence analyses will be performed. Test–retest reliability analyses will estimate the impact of learning effects on performance, and compare remote administration with in-person delivery of the assessment.

#### MRI substudy

Clinically acquired brain imaging at the time of the acute stroke (including fluid-attenuated inversion recovery (FLAIR) and diffusion-weighted imaging sequences) will be obtained. All 300 patients will be invited to undergo additional brain MRI imaging at 3 and 12 months using a Siemens Verio 3T scanner at the Imperial College Clinical Imaging Facility. MRI measures will be used as prognostic indicators for cognitive trajectory. MRI data will be collected from additional 50 age-matched control participants for comparison. The following sequences will be acquired at each session over 60–90 min (breaks included):

Structural MRI: T1 (1 mm^3^ resolution for volumetric analyses of lesion volume and brain atrophy); susceptibility weighted imaging (0.8×0.8×3.0 mm^3^ for identification of microbleeds); T2 FLAIR (1 mm^3^ for detecting white matter hyperintensity volume (WMHV)); and neurite orientation dispersion and density imaging (NODDI, an advanced multishell diffusion MRI with 90 directions and 9 b_0_ images) to assess axonal integrity and tissue microstructure. Lesions will be defined using established standards.^17^Functional MRI: Resting-state and breath-hold paradigm will measure dynamic regional brain activity and vascular reactivity, respectively.^18^

#### Blood biomarkers substudy

Blood samples will be obtained at baseline (0–15 days poststroke), and at 3, 6 and 12 months from 200 patients. Two EDTA (plasma) and two Serum-Seperating Tube samples will be collected. Sample processing involves centrifugation at 2000 g for 10 min at 4°C, followed by secure storage at −80°C. Additional single PAXgene sample will be collected at one time point for DNA storage for future analysis of apolipoprotein E genotype and polygenic risk score measures. The patient’s identity is kept confidential. The primary plasma biomarker of interest will be NFL.^19^ Additional markers including GFAP (for astrocytic activation^20^), brain-derived τ (a novel marker for neuronal injury^21^), phosphorylated τ forms and Aβ42/40 ratio (both biomarkers for Alzheimer’s pathologies^22^) will be quantified. Testing will be performed at University College London via a Quanterix Simoa analyser to provide ultrasensitive measurement of concentrations.

### Patient and public involvement statement

The IC3 assessment was developed and refined during a 6 months iterative process of design modifications based on patient and user feedback. We conducted feedback sessions with stroke survivors part-way through the development of our assessment to ensure that (1) our cognitive assessments are intuitive, (2) the instructions are comprehensible, (3) patients can complete the assessment with minimum supervision and (4) the burden of assessments are acceptable. Based on these sessions, we made several improvements to the design of the assessment, primarily focusing on improving the user interface, user experience and the instructions. We also involved multiple age-matched members of the public, without a diagnosis of stroke, to ensure that our design changes were effective and to identify any issues with performing the assessment remotely. Finally, we disseminated the study design through local public outreach events (eg, educational events for older adults, health advocacy charities) and incorporated the received feedback in the end product.

### Study population

#### Participant identification, recruitment

Online supplemental table 1 outlines the patient inclusion and exclusion criteria. Patients will be recruited from the Imperial College Healthcare NHS Trust by study personnel and the clinical team. Our goal is to recruit patients as early after stroke as is practical, and ideally within 15 days to facilitate acute blood biomarker assessment. Control participants will be aged >18 and without history of neurological or severe psychiatric illness.

10.1136/bmjopen-2023-076653.supp1Supplementary data

### Outcome measures

The primary outcome measure for cognition will be the IC3-derived accuracy measures for each primary cognitive domain listed in table 1 at 1-year post ictus. Secondary outcome measures will be (a) MOCA score,^15^ (b) functional measures including National Institute of Health Stroke Scale,^23^ Modified Rankin Scale,^24^ Instrumental Activities of Daily Living^14^ and (c) psychological measures via the Geriatric Depression Scale^13^ and Apathy Evaluation Scale.^7^

### Data analysis plan

#### Cognition

Dimensionality reduction techniques, such as principal component analysis, graph-based methods and hierarchical clustering will examine the inter-relationship between cognitive domains and will be used to derive latent variables. These will be used to relate to blood and imaging biomarkers. Such cognitive profiling will also form the basis for future real-time optimisation of the IC3 task presentation based on patients’ performance.

To assess the trajectories of functional, clinical and psychological outcome measures, we will employ linear mixed effect models. These models will include cognitive measures as the main predictors, together with standard covariates such as age, sex, lesion and initial cognitive deficit.

#### Blood biomarkers

NFL, GFAP, amyloid and tau biomarkers will be analysed to describe their dynamics after acute stroke and to compare differences between groups. Additionally, longitudinal changes in these biomarkers will be assessed within patients using non-parametric tests, where appropriate. The relationship between blood biomarker levels and continuous outcome measures at 1 year (eg, cognitive scores) will be investigated using mixed-effects linear regression. For binarised outcome measures (eg, favourable or unfavourable MRS scores), logistic regression will be employed.

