#### Sample size

The primary blood biomarker predictor is NFL. Based on preliminary reported group differences,^19^ we expect 140 patients at baseline, and 60 patients at 3-months poststroke (when peak NFL is expected to occur), will be able to detect group differences in NFL levels between patients and controls (Wilcoxon Mann Whitney test, Cohen’s d=0.38 and 0.58, respectively, alpha=0.05, power=0.8, one tailed, allocation ratio 2:1). A much smaller sample size of 56 will be enough to detect correlations between NFL and time of sampling of the acute blood: (r^2^=0.10,^19^ alpha=0.05, power=0.8, one tailed).

The primary imaging outcome measure is WMHV. A sample size of 80 will be sufficiently powered to detect correlation between NFL and WMHV based on preliminary findings^25^ (r=0.32, alpha 0.05, power 0.95). A sample size of N=70 will be sufficiently powered to detect the relationship between peak plasma NFL levels and binary functional outcomes (based on similar effects observed after acute brain injury (R^2^=0.28,^26^ α=0.05, power=0.9). Expecting a 20%–25% lost to follow-up rate (due to patient factors and technical factors), the stated sample size of 200 in blood biomarker substudy is sufficiently powered to detect all the above-mentioned effects.

A secondary blood biomarker predictor is raised phosphorylated tau. Based on the mean and SD reported for longitudinal change in phosphorylated tau (N=374) in population of elderly cognitively normal population,^27^ a sample size of N=65, will have 95% power in detecting any true change in mean over 1-year period (α=0.05, effect size 0.41). Thus, the stated sample size is sufficiently powered to detect longitudinal change in phosphorylated tau.

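### For within-patient biomarker change the article names only non-parametric tests, which ignore actual sampling time and estimate no trajectory, although the time course is a stated aim

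*Protocol article*

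**What the plan says.** The Aims section of the protocol article states: "The study will characterise the time course of these biomarkers over the first year after stroke". The Blood biomarkers substudy section sets the design: "Blood samples will be obtained at baseline (0–15 days poststroke), and at 3, 6 and 12 months from 200 patients".

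The Blood biomarkers part of the Data analysis plan has three elements:

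- A general statement, with no method attached: "NFL, GFAP, amyloid and tau biomarkers will be analysed to describe their dynamics after acute stroke and to compare differences between groups".
- An additional statement on change: "longitudinal changes in these biomarkers will be assessed within patients using non-parametric tests, where appropriate". No test is named.
- A model relating biomarkers to outcome rather than to time: "continuous outcome measures at 1 year (eg, cognitive scores) will be investigated using mixed-effects linear regression".

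On timing, the Figure 3 caption adds: "The 1-year follow-up is expected to take place between 12 months and 24 months poststroke". On attrition, the Sample size section gives one rate: "Expecting a 20%–25% lost to follow-up rate (due to patient factors and technical factors".

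Elsewhere the plan uses linear mixed models for functional, clinical and psychological trajectories (Cognition). For longitudinal imaging it uses linear regressions that account for age, sex, initial severity, lesion volume and time (Brain imaging).

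**The concern.** The only method named for within-patient biomarker change does not yield the quantity that the aim asks for. A Wilcoxon signed-rank test or a Friedman test asks whether levels differ between labelled visits. It gives no fitted course, cannot use the actual sampling day, and in standard form takes no covariates.

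The article's own figures suggest that sampling time matters. The Sample size section powers a correlation between NFL and the time of the acute blood draw (r² = 0.10), so NFL is expected to vary inside the 0–15 day baseline window. The same section expects NFL to peak at 3 months. A rise and fall of this kind is described by a function of time, not by a test of difference.

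Attrition is the secondary issue. A test that needs all four samples discards the remaining samples of any patient who misses a visit. If those who leave differ in stroke severity from those who stay, comparisons among completers could mislead.

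**Working it through.** **Inputs from the article.** 200 patients; four samples (baseline, 3, 6 and 12 months); loss L = 20% to 25%. The only sample size for within-patient biomarker change is phosphorylated tau: N = 65, power 0.95, alpha 0.05, effect size 0.41, sidedness not stated.

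**1. The plan's own figure.** For a paired mean change, n = ((z for alpha + z for power)/d)².

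- One-sided: ((1.645 + 1.645)/0.41)² = 64.4, so 65 (66 with the t distribution). The stated figure is reproduced.
- Two-sided: ((1.960 + 1.645)/0.41)² = 77.3, so 78 (80 with the t distribution). The stated figure is not reproduced.

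The figure of 65 is therefore consistent with a one-sided test of a change in mean.

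**2. Patients left for a four-visit complete-block test.** Reading the loss as cumulative by the last visit, complete sets = 200 × (1 − L):

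- L = 20%: 200 × 0.80 = 160.
- L = 25%: 200 × 0.75 = 150.

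**3. Samples discarded.** Assumption: cumulative loss accrues evenly over the three follow-ups, so the fractions present are 1, 1 − L/3, 1 − 2L/3 and 1 − L. Samples collected = 200 × (4 − 2L). Samples used by a complete-block test = 4 × 200 × (1 − L).

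| L | Collected | Used | Discarded |
|---|---|---|---|
| 20% | 200 × 3.6 = 720 | 640 | 80/720 = 11% |
| 25% | 200 × 3.5 = 700 | 600 | 100/700 = 14% |

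**4. Pairwise tests instead.** Under the same assumption, baseline to 3 months keeps 200 × (1 − L/3) = 187 to 183 patients. Baseline to 6 months keeps 200 × (1 − 2L/3) = 173 to 167. Baseline to 12 months keeps 160 to 150, the same as the complete block. Pairwise testing therefore drops fewer patients at the earlier visits only.

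**5. Power for phosphorylated tau.** This uses the noncentral t. The signed-rank test is approximated by the relative efficiency 3/π, which assumes normally distributed changes. With 150 patients and a two-sided test, power at effect size 0.41 is 0.999 for the t test and 0.998 for the signed-rank test. One-sided power is higher. The stated power survives.

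**6. Timing.** With visit labels, a sample on day 0 and one on day 15 count as the same time point. So would samples at 12 and 24 months, if blood is drawn at the 1-year follow-up as the Figure 3 caption describes it. The substudy section itself gives 12 months.

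**The case against.** The strongest reply is that the sentence is open. It is introduced as an addition, is qualified to apply only where suitable, and follows a separate promise to describe the dynamics. The article also plans one analysis in which acute sampling time is continuous. This stands to a degree: a reader might infer that rank tests are fixed as the sole method, or that the plan cannot describe a time course at all, and the text supports neither. Still, the promise to describe dynamics carries no method, and the qualifier names no alternative.

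Second, a reader might infer that incomplete patients will be dropped. No test is named, so this is inference. It holds for a Friedman-type test. Signed-rank tests drop only patients missing one of the two visits compared, and rank methods for incomplete blocks exist.

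Third, a reader might apply the loss rate afresh at each follow-up, leaving 200 × 0.80³ = 102 or 200 × 0.75³ = 84 complete patients. The article gives one rate, set against the total of 200, and says nothing of independent loss at each visit. That reading is not supported.

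Fourth, the lack of covariates is a weak complaint about a within-patient comparison, because stable factors such as age and sex cancel.

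Fifth, full model specification commonly sits in a protocol or analysis plan not shown here. That is fair as to detail. The point is that the method the article does name for change does not estimate a trajectory, while the article names regression or mixed models for its other longitudinal analyses.

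**Conclusion.** The concern holds in a limited form. For within-patient biomarker change the article names only non-parametric tests. In their standard form these ignore actual sampling time and estimate no trajectory, so they do not by themselves serve the time-course aim.

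The data cost is moderate. A four-visit complete-block test would use 150 to 160 of 200 patients and discard about 11–14% of samples. This rests on cumulative loss of 20–25% spread evenly over the follow-ups, a pattern that the article does not state. Bias from dropping incomplete patients is possible but cannot be sized from the document.

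A reader might conclude that the substudy becomes underpowered. It does not: at 150 patients, power for the phosphorylated tau change stays above the stated 0.95 with either test. This is a worthwhile, inexpensive improvement to the analysis, not an error that defeats a stated objective.

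**What to change.** Make the main analysis of within-patient biomarker change a linear mixed model of log concentration. Include a patient random intercept, a flexible function of actual days since stroke (for example a spline), and age, sex and lesion volume as covariates. As main effects these covariates shift the level only, so add lesion volume by time if change is to depend on it. Use all available samples, and keep the non-parametric paired tests as a sensitivity check.

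The cost is a change of analysis wording. It needs no new data beyond the date of each sample, and mixed models are already planned elsewhere in the article. Under the even-loss assumption the model would use all 700 to 720 samples instead of 600 to 640, although a patient with only a baseline sample adds no direct information on change.

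There are two downsides. The model assumes a distribution on the log scale. It also assumes data missing at random, which does not cover dropout that depends on unobserved values.
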